## Abstract

**Background:**

The goal of radical prostatectomy is to achieve the optimal balance between complete cancer removal and preserving a patient’s urinary and sexual function. Performing a wider excision of peri-prostatic tissue helps achieve negative surgical margins, but can compromise urinary and sexual function. Alternatively, sparing peri-prostatic tissue to maintain functional outcomes may result in an increased risk of cancer recurrence. The objective of this study is to determine the effect of providing surgeons with detailed information about their patient outcomes through a surgical report card.

**Methods:**

We propose a prospective cohort quasi-experimental study. The intervention is the provision of feedback to prostate cancer surgeons via surgical report cards. These report cards will be distributed every 3 months by email and will present surgeons with detailed information, including urinary function, erectile function, and surgical margin outcomes of their patients compared to patients treated by other de-identified surgeons in the study. For the first 12 months of the study, pre-operative, 6-month, and 12-month patient data will be collected but there will be no report cards distributed to surgeons. This will form the pre-feedback cohort. After the pre-feedback cohort has completed accrual, surgeons will receive quarterly report cards. Patients treated after the provision of report cards will comprise the post-feedback cohort. The primary comparison will be post-operative function of the pre-feedback cohort vs. post-feedback cohort. The secondary comparison will be the proportion of patients with positive surgical margins in the two cohorts. Outcomes will be stratified or case-mix adjusted, as appropriate. Assuming a baseline potency of 20% and a baseline continence of 70%, 292 patients will be required for 80% power at an alpha of 5% to detect a 10% improvement in functional outcomes. Assuming 30% of patients may be lost to follow-up, a minimum sample size of 210 patients is required in the pre-feedback cohort and 210 patients in the post-feedback cohort.

**Discussion:**

The findings from this study will have an immediate impact on surgeon self-evaluation and we hypothesize surgical report cards will result in improved overall outcomes of men treated with radical prostatectomy.

**Electronic supplementary material:**

The online version of this article (10.1186/s12894-018-0403-y) contains supplementary material, which is available to authorized users.

## Background

Prostate cancer and the side effects of treatment are major public health issues, since the disease is diagnosed in approximately 18% of men [1]. The vast majority of patients diagnosed currently have localized disease that can be cured surgically with radical prostatectomy [2–4]. Since the prostate is in close proximity to the urethral sphincter and nerves that facilitate erections for sexual function, these structures are often inadvertently injured or purposefully resected during tumour resection. Consequently, approximately 0.3–12.5% of men suffer permanent urinary incontinence after a radical prostatectomy, and up to 30% of men use incontinence pads [5–8]. It is also estimated that 75% of patients will suffer from temporary or permanent erectile dysfunction following a radical prostatectomy [9, 10]. Maintenance of urinary and erectile function is related to surgical technique, and significant differences in function following radical prostatectomy have been observed between surgeons [11–13].

Positive surgical margins occur in approximately 11–38% of patients [14, 15]. A positive surgical margin can be an indication of locally-advanced disease, but is also a reflection of surgical technique. Surgical margin rate has been highlighted as an indicator of surgical quality that should be monitored prospectively [16] Significant variability exists in positive margin rates between surgeons [2, 11, 17, 18]. The surgical margin status of a patient is important because this outcome is highly associated with increased need for secondary salvage treatments and lower overall survival [19–21].

In a 2006 provincial pathology audit, positive surgical margins were found in 33% of patients who had tumours that did not extent outside the prostate (pathologic stage T2) in Ontario, Canada (population 12,160,282). In 2008, a Cancer Care Ontario expert clinician panel set a provincial goal to reduce the incidence of positive surgical margins to less than 25% [22]. Since that time, Cancer Care Ontario has been providing feedback to clinicians on the incidence of positive surgical margins in their patients. As of 2011, the incidence of pT2 positive surgical margins in Ontario had dropped to 21% [23]. This finding supported the hypothesis that prospective reporting and feedback can affect surgeon behaviour, resulting in improvement. The findings in Ontario are consistent with randomized trials that show feedback to clinicians generally result in practice improvement [24].

A potential negative consequence of surgical margin scrutiny by Cancer Care Ontario is that surgeons may be performing a wider excision of peri-prostatic tissue, purposely sacrificing erectile nerve tissue to lower the risk of a positive margin, and as a result compromise urinary and sexual function. Clearly, a balance must be struck between ensuring complete cancer removal and preservation of a patient’s urinary and sexual function. Isolated critical evaluation of surgical margin rates may have had the unintended effect of increasing long term side effects that are important to patients. Ideally, all clinically important outcomes should be assessed when evaluating surgical quality, not only surgical margin status.

The primary purpose of this study is to determine if providing prostate cancer surgeon feedback on their patients’ improves overall surgical quality as measured by surgical margin rates and patient reported functional outcomes.

## Methods

### Study design and setting

This is a prospective cohort quasi-experimental before-and-after study at The Ottawa Hospital. The Ottawa Hospital is an academic hospital affiliated with the University of Ottawa. The Ottawa Hospital serves the Champlain Local Health Integration Network (LHIN), which is a geographic boundary that contains a population of approximately 1.3 million people [25]. Approximately 80% of prostate cancer patients in the Champlain LHIN who receive a radical prostatectomy are treated by one of eight prostate cancer surgeons at the Ottawa Hospital. The intervention in this study is the provision of feedback to prostate cancer surgeons via surgical report cards. These report cards will be distributed every 3 months by email. The report card will present surgeons with outcomes of their patients compared to patients treated by other de-identified surgeons in the study.

### Study participants

All prostate cancer surgeons will participate in this study. While all surgeons will use a common clinical pathway and provide consistent information, the surgical technique is not mandated by the study. All patients undergoing radical prostatectomy by each surgeon will be eligible, regardless of tumour stage, histology and previous pelvic treatments including surgery or radiation. Extent of planned and performed neurovascular bundle preservation will not be mandated, but will be prospectively collected from the operating surgeon. Surgeons will report their nerve spare intent prior to surgery and their perceived nerve spare achieved following surgery. All surgical approaches (open, laparoscopic, and robotic assisted laparoscopic) will be included. Given that patients are contacted for assessment of symptoms, consent will be obtained from each patient. Patients will be excluded if they 1) decline or are incapable of providing consent; 2) are less than 18 years of age; or 3) are being treated outside of The Ottawa Hospital. Patient information and outcomes will be collected prior to surgery and 6- and 12-months following surgery. Approximately 230 radical prostatectomy procedures are performed annually at The Ottawa Hospital.

### Assessment and data collection

#### Pre-surgery

Prior to treatment, patients will complete two functional assessments that were selected based on content validity, common use in clinical practice, and availability in English and French: (1) The Expanded Prostate Cancer Index Composite (EPIC), and (2) the EQ-5D. EPIC is a 50-item robust and comprehensive prostate cancer-specific instrument that measures a broad spectrum of urinary, bowel, sexual, and hormonal symptoms. The EPIC has been widely validated and used in prostate cancer clinical trials and treatment quality initiatives [26] and will serve as the basis for urinary and erectile function assessment. EQ-5D is a simple, easy to use assessment of overall health status and provides a descriptive profile and a single index value for reporting [27]. The EQ-5D is valid and reliable across a broad range of clinical settings and languages.

Other pre-operative baseline characteristics will be collected, including patient age, height, weight, clinical tumour stage, tumour grade, and prostate specific antigen (PSA) concentration. This information is available from the standardized pre-operative pathway documents and will be abstracted by study personnel.

#### Time of surgery

Synoptic reporting will be used by surgeons and pathologists to aid with data collection. Surgeons will document planned and achieved preservation of neurovascular bundles. Pathology reports will be used to determine cancer stage, tumour grade, tumour size, location of extraprostatic tumour extention (if applicable), extent of extraprostatic tumour extension (if applicable), location of a positive surgical margin (if applicable), and extent of a positive surgical margin (if applicable).

#### Post-surgery

At 6 and 12 months post-operative, patients will be mailed the same quality-of-life and functional assessment questionnaires that were completed prior to surgery. Study personnel will contact patients who do not return the questionnaires to facilitate completion or to determine why the patient does not wish to participate. This duration of follow-up was chosen because functional outcomes improve over time and most outcomes have generally stabilized by 12 months post-surgery [28]. Post-operative interventions that could confound results will be determined by asking patients if they currently use erectile function aids, have had urinary continence procedures, received pelvic radiation, or received androgen deprivation. All post-operative PSA values will be documented.

### Surgical report card intervention and control

Descriptive baseline, pathological, and follow-up information will be summarized and tabulated. The primary measures of surgical quality on the surgeon report cards will be: post-operative urinary continence, post-operative erectile function (stratified by baseline function and tumour stage), and rate of positive surgical margins (stratified by tumour stage). An example of a surgical report card is displayed in Additional file 1. Urinary continence will be defined as requiring no continence pads (i.e. score of 0 on question 5 of the EPIC questionnaire), and potency will be defined as a firm enough erection for intercourse (score of 4 on question 18 of the EPIC questionnaire). Changes in patients’ overall health status will also be summarized.

For the pre-feedback cohort, pre-operative, 6-month, and 12-month patient data will be collected but there will be no report cards distributed to surgeons. This will form the pre-feedback cohort. When accrual to the pre-feedback cohort is complete (anticipated to be 12 months from initiation of the study), surgeons will begin receiving report cards. Patients treated after the provision of report cards will form the post-feedback cohort for analyses. A summary of the study timeline is presented in Fig. 1.

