### Outcomes

The primary outcomes will be post-operative function of the patient cohort before surgeon feedback (pre-feedback cohort) compared to post-operative function of the patient cohort after surgeon feedback (post-feedback cohort). The secondary comparison will be the proportion of patients with positive surgical margins in the pre-feedback cohort compared to post-feedback cohort. Outcomes will be stratified or adjusted by important co-variates such as patient age, tumour stage, tumour grade, pre-operative PSA, baseline urinary function, baseline sexual function, and nerve preservation status.

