### Analysis and sample size

The comparison between pre-and post-feedback functional outcomes will be done by using generalized linear model that treats the intervention as an effect that is either present or absent for a patient (absent for the pre-feedback cohort and present the post-feedback cohort). In the analysis the surgeons will be considered as clusters to account for repeated measurements. In the model other covariates like patient age, tumour stage, tumour grade, pre-operative PSA, baseline urinary function, baseline sexual function, and nerve preservation status will be used. An estimate of the difference between pre-feedback and post-feedback potency or continence will be obtained from the above model.

An overall improvement of 10% in potency or incontinence following the surgeon feedback intervention (post-intervention cohort) will be considered clinically significant. Assuming a baseline potency of 20% and a baseline continence of 70%, 294 patients would be required for 80% power at an alpha of 5%. Assuming as much as a 30% lost to follow up, we will require a minimum of 210 patients in the pre-feedback cohort and 210 patients in the post-feedback cohort.

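### Continence and potency are scored without regard to later procedures or aids, and report cards start while pre-feedback patients are still in follow-up

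*Protocol article*

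**What the plan says.** Under Surgical report card intervention and control, the article fixes two binary measures. For continence: "Urinary continence will be defined as requiring no continence pads (i.e. score of 0 on question 5 of the EPIC questionnaire". For potency: "potency will be defined as a firm enough erection for intercourse (score of 4 on question 18 of the EPIC questionnaire". Neither carries a condition on how the function was obtained. The same section presents these measures as indicators of surgical quality on the cards, and the functional comparison in Analysis and sample size is made on potency and continence.

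Under Post-surgery, the article says: "Post-operative interventions that could confound results will be determined by asking patients if they currently use erectile function aids, have had urinary continence procedures". Pelvic radiation and androgen deprivation are collected for the same reason.

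Under Analysis and sample size, the adjustment variables are introduced as follows: "In the model other covariates like patient age, tumour stage, tumour grade, pre-operative PSA, baseline urinary function, baseline sexual function", with nerve preservation status added. The Outcomes section gives the same list. Both lists are illustrative rather than closed, and neither names a post-operative intervention.

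On timing: "When accrual to the pre-feedback cohort is complete (anticipated to be 12 months from initiation of the study), surgeons will begin receiving report cards". Cohort membership follows the date of treatment, and the model carries one present-or-absent feedback term. Questionnaires are mailed 6 and 12 months after surgery.

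**The concern.** There are two separate issues, and they should be kept apart.

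The first is the outcome definition. The Background states the aim as surgical quality, and Post-surgery treats later procedures and aids as something that could distort the results. Yet the definitions pass over them. A man who leaked until he had a continence procedure and now wears no pad meets the continence definition. A man who reaches the potency score only with an aid meets the potency definition. If the frequency of such cases differs between the cohorts, the comparison picks up that difference as if it came from the operation.

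The second is the timing of the comparator. The surgeons who begin to receive cards at about month 12 are the surgeons of pre-feedback men who are still in follow-up. The operation on those men cannot be changed by the cards, but their aftercare can. The two issues push in opposite directions: changed aftercare in the post-feedback cohort could imitate a surgical gain, while the same change among pre-feedback men could hide one. A single feedback indicator set by treatment date cannot separate them. Surgical margins are fixed at operation and are not affected.

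**Working it through.** **1. Definitions against collected items.**

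| Item | Collected at follow-up | In the outcome definition | In the named covariates |
|---|---|---|---|
| Continence procedure (ever had) | yes | no | no |
| Erectile aid (current use) | yes | no | no |

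The open wording of the covariate lists would allow both items to be added, but that would not settle the matter. They arise after surgery and may lie on the path from feedback to outcome, so conditioning on them does not recover the effect of the operation. For procedures the remedy belongs in the definition.

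**2. Questionnaire dates against card start.** Inputs: accrual over T = 12 months (anticipated in the article), cards from month T, questionnaires at 6 and 12 months. Assumption: uniform accrual. For a man operated on at month s, with s between 0 and T:

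- The 12-month questionnaire falls at s + 12, which is at or after T if s ≥ T − 12. The share is min(1, 12/T) = 12/12 = 100%. Time already under cards is s + 12 − 12 = s, so 0 to 12 months, mean 6.
- The 6-month questionnaire falls at s + 6, which is at or after T if s ≥ T − 6. The share is min(1, 6/T) = 6/12 = 50%. For these men, time under cards is s − 6, so 0 to 6 months, mean 3.

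**3. Sensitivity to accrual time.** The article gives about 230 operations a year and a minimum of 210 men per cohort, so T = 12 × 210 / (230 × consent rate). The consent rates are assumptions.

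| Consent | T (months) | 12-month forms after card start | 6-month forms after card start |
|---|---|---|---|
| 100% | 10.96 | 100% | 55% |
| 90% | 12.2 | 99% | 49% |
| 80% | 13.7 | 88% | 44% |
| 70% | 15.7 | 77% | 38% |

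**4. What could follow, as illustration only.** The documents give no rate of aid or procedure use and no evidence on aftercare, so every input here is assumed.

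- Aided potency with no change in surgery: at 20% baseline potency, 80% are not potent. If aid uptake among them rises by 10 to 30 points and 20% to 60% of the added users respond, apparent potency rises by 0.80 × 0.10 × 0.20 = 1.6 points to 0.80 × 0.30 × 0.60 = 14.4 points. The article's clinically significant difference is 10 points.
- Leakage into the comparator: if 10%, 25% or 50% of a true 10-point gain also reaches pre-feedback men, the difference shrinks to 9, 7.5 or 5 points. Two-sided power for potency (pooled-variance test of two proportions, alpha 5%, no allowance for clustering or covariates) is then:

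| Evaluable per cohort | No leak | 10% | 25% | 50% |
|---|---|---|---|---|
| 147 (= 210 × 0.70) | 51% | 42% | 31% | 16% |
| 294 | 80% | 71% | 54% | 27% |

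Leakage of this kind needs part of the gain to come through aftercare. A gain made wholly in the operating room cannot leak.

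**5. Power of a restricted 6-month comparison.** Half of 147 is about 73 pre-feedback men, against 147 post-feedback men. By the same test, two-sided power for a 10-point difference is about 34% for potency (20% to 30%) and 38% for continence (70% to 80%).

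**The case against.** The strongest reply has several parts.

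- **Nothing shows that aftercare changes.** This stands. The article also says that all surgeons will follow a common clinical pathway, which plausibly limits differences in aftercare, though it does not rule out drift. The same definitions apply to both cohorts, so aided function biases the comparison only if its frequency changes between them.
- **The 100% counts dates, not exposure.** This stands. A reader might infer that the whole comparator is fully exposed to feedback. It is not: time under cards before the 12-month form runs from 0 to 12 months, and the earliest patients have almost none. The first cards also carry few functional results, because almost no 12-month results exist yet.
- **The handling may sit in an unseen analysis plan.** This stands in part. The covariate lists are open and the confounders are collected. But the article does state the outcome definitions, and covariates would not repair them.
- **A total effect of feedback, aftercare included, is a legitimate target.** This is fair, since the Background measures quality by patient-reported function. Against it, the article itself calls these interventions possible confounders.
- **Unaided potency as the main definition would bring its own bias.** This stands. Only current aid use is recorded, not need. A man who would reach the score unaided but uses an aid would become a failure, and if feedback raised aid use, post-feedback potency would fall artificially. Potency should therefore not be redefined on this ground. Continence procedures differ, because the item asks whether one has been done.

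**Conclusion.** The point holds as a limited one. The definitions let a man who is dry only after a corrective procedure count as a surgical success, although the article collects that information and says that it could confound the results. On the anticipated 12-month accrual, essentially all pre-feedback 12-month questionnaires and about half of the 6-month ones are completed at or after card start. The first share falls to 88% or 77% if accrual runs to 13.7 or 15.7 months.

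A reader might go further and infer that the study will mistake aftercare for surgery, or that its comparison is biased by a known amount. The documents do not support that. They report no change in aftercare and give no rates, and the two mechanisms oppose each other. The illustrative figures only show what the stated assumptions would imply. The conclusion is an uncontrolled risk of unknown size and net direction, with inexpensive improvements available.

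**What to change.** 1. In Surgical report card intervention and control, define continent as no pads and no continence procedure since surgery, so that a man who needed a procedure counts as not continent.
2. Keep potency as defined. Add a supporting analysis of the same score without current aid use, and state that it misclassifies men who use an aid but do not need it.
3. Add a supporting comparison of 6-month function in which the comparator is limited to pre-feedback men whose 6-month questionnaire was completed before the first card.

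The cost is one reworded definition and two supporting analyses, with no new data. The 70% continence assumption may need restating under the new definition; the documents do not allow the shift to be estimated. The restricted 6-month analysis uses about half of the comparator, has low power and should be read as descriptive. It does not repair the 12-month comparison, and the article itself treats 12 months as the point by which most outcomes have settled. The report should therefore say that pre-feedback 12-month outcomes were collected while surgeons were already receiving cards.

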**Fig. 1 Fig1:**
[figure not shown]
Study timeline

### Outcomes

The primary outcomes will be post-operative function of the patient cohort before surgeon feedback (pre-feedback cohort) compared to post-operative function of the patient cohort after surgeon feedback (post-feedback cohort). The secondary comparison will be the proportion of patients with positive surgical margins in the pre-feedback cohort compared to post-feedback cohort. Outcomes will be stratified or adjusted by important co-variates such as patient age, tumour stage, tumour grade, pre-operative PSA, baseline urinary function, baseline sexual function, and nerve preservation status.

